## Methods/design

### Trial design

This study is a two-armed, parallel-group RCT, using a 1:1 allocation ratio, designed to investigate whether coaches who attended coach education sessions (where education on increasing MVPA and decreasing inactivity during training was delivered) can increase their players’ MVPA during training sessions over a 5-day basketball program; compared to coaches who did not receive coach education sessions (Figure 1). Outcomes were assessed at baseline (day 1 of the basketball program) and follow up (day 5 of the program). The Human Research Ethics Committee of the University of Western Sydney (UWS) approved this study. This study adheres to the Consolidated Standards of Reporting Trials guidelines [16].

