### Sample size and power calculation

On the basis of an α of 0.05 and 80% power to detect a significant differential change in MVPA between groups, using an effect size of *d* = 0.6, a minimum sample size of 36 female players for each group was needed (*N* = 72). Our effect size is consistent with the findings of a recent systematic review and meta-analysis of interventions designed to increase children and adolescents’ MVPA in a similar setting (physical education), *d* = 0.62 [18]. To protect against player attrition and preserve adequate statistical power, the sample size was inflated by 10%, thus a total sample of 80 female players was sought.

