### Statistical analysis

All variables will be checked for normality using the Shapiro-Wilk test. Independent samples *t-*tests or Mann–Whitney *U-*tests will then be conducted, as appropriate, to examine: (1) baseline differences between groups and (2) baseline differences between players who completed the study and those lost to follow-up. If variables significantly differ between groups, they will be appropriately adjusted in the main analyses.

Linear mixed models will be used to analyse the differential change between groups on all outcomes from baseline to follow-up, using baseline data as the covariate. Linear mixed models will be used because these models are robust enough to withstand the biases from missing data, and provide good control of Type I and Type II errors [50]. All analyses will be conducted using SPSS 21.0 (Chicago, IL, USA). The level of significance will be set at *p* < 0.05.

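### The stated robustness to missing data does not apply: with day 1 as covariate and day 5 as the only follow-up, the mixed model treats dropouts as a complete-case ANCOVA does

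*Protocol article*

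**What the plan says.** Trial design fixes two assessment points: "Outcomes were assessed at baseline (day 1 of the basketball program) and follow up (day 5 of the program"). Statistical analysis compares the arms on change between these two points by linear mixed models, "using baseline data as the covariate", for every outcome. One of its two reasons for the model is missing data: "Linear mixed models will be used because these models are robust enough to withstand the biases from missing data". The other is control of Type I and Type II error.

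Sample size and power calculation expects some loss: "the sample size was inflated by 10%, thus a total sample of 80 female players was sought".

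Table 2 (Study procedure) lists accelerometry on days 1–5. The Accelerometry section has the device worn throughout each program day, with start and finish times of training sessions recorded. Motivation and perceived autonomy support are collected on days 1 and 5 only. Statistical analysis does not bring days 2–4 into the outcome comparison. It does plan a baseline comparison of players who complete the study with those who do not.

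**The concern.** A mixed model gains from incomplete cases through the other outcome records of the same player. In the analysis described there are none: day 1 is on the right-hand side and day 5 is the only outcome day. A player missing on day 5 has no outcome row, so the model has nothing to borrow from, and the reason given for choosing it is not earned.

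This matters if girls who leave before day 5 differ in ways that their baseline does not capture, for example in how active they were on days 3 and 4 under their allocated coaches. A report following this plan could claim protection against such dropout without having it, although the activity data that would give it are on the accelerometers.

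**Working it through.** **1. The plan's own figure.** The plan needs 72 players and allows 10% loss. 72 / (1 − 0.10) = 80, and 72 × 1.10 = 79.2, which also leads to 80. The stated 80 reproduces. A loss of 0.10 × 80 = 8 leaves the planned 72. (The 36 per arm behind the 72 reproduces for d = 0.6 only with a one-sided test. That is a separate matter and has no bearing here.)

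**2. What the described model does with a dropout.** Write it as y5 = β0 + β1·arm + β2·y1 + b + e, with a player random intercept b and one record per player. The covariance matrix is V = (σb² + σe²)·I, so the scale factor cancels and the generalised least squares estimate is (X′X)⁻¹X′y. This is ordinary ANCOVA on players who have day 5. In a simulated set of 80 players, 72 of them with day 5, ANCOVA gave an arm coefficient of 0.32088. The mixed model gave 0.32088 with random-intercept variances of 0.1, 0.5 and 0.9 (residual variance 0.6).

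**3. Variants of the description.** With the two day-5 training sessions as separate records, or with coach or site random effects, the model is no longer literally an ANCOVA. A player absent on day 5 still has no row. If day 1 were instead placed in the outcome with an arm-by-time term, the dropout would supply only the day-1 value. Step 4 shows that this adds no protection.

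**4. What could follow.** A simulation of 400,000 players, with these assumptions, none of them in the documents: SD 1; half the variance between players; autoregressive correlation of 0.6 between days for the other half; true arm effects of 0, 0.2, 0.6, 0.6, 0.6 on days 1 to 5. The implied correlation is 0.5 + 0.5 × 0.6 = 0.80 between days 4 and 5, and 0.5 + 0.5 × 0.6⁴ = 0.565 between days 1 and 5. Only day 5 can be missing. The days 1–5 estimate regresses day 5 on arm and days 1–4 among those observed, predicts for all players, and then adjusts for day 1. The true day-5 effect is 0.60.

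| Day-5 dropout depends on | Missing | Complete-case ANCOVA | Days 1 and 5 jointly | Days 1–5 |
|---|---|---|---|---|
| baseline and arm | 9.0% | 0.601 | 0.602 | 0.602 |
| day-4 activity, opposite direction by arm | 8.4% | 0.675 | 0.675 | 0.602 |
| day-4 activity, intervention arm only | 7.4% | 0.645 | 0.646 | 0.602 |
| the unseen day-5 value, intervention arm only | 7.4% | 0.665 | 0.665 | 0.635 |

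The simulation error is at most about 2/√364,000 = 0.003, so 0.601 and 0.602 count as unbiased. In rows two and three, ANCOVA is off by 0.075 and 0.045, or 12.5% and 7.5% of 0.60, and the days 1–5 analysis is not. In row four both are off, by 0.065 and 0.035.

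**The case against.** The best case for the plan has four parts.

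- Complete-case ANCOVA is unbiased when dropout depends only on arm and modelled baseline covariates, as the first row of the table shows. The planned baseline comparisons, with adjustment for variables that differ, may extend that set of covariates. This stands. It does not reach dropout driven by activity after day 1, which a baseline comparison cannot see.
- Dropout may be small and harmless: the camp lasts five days, players had to intend to stay for all of it, they were blinded to allocation, and the sample already covers a loss of 8. This stands as a reason not to predict a bias. It secures power, and does not make the quoted reason true.
- Day 2 falls between the two coach education sessions, and a day-1-to-day-5 contrast is a legitimate target. Both are right. With a free arm effect on each day, the earlier days inform the missing day-5 values without altering the target.
- Random effects, covariance structure and missing-data assumptions may sit in a fuller plan. Agreed; their absence is not the point. The point is a reason that the article does state.

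Three stronger readings are tempting, and the documents do not support them. A reader might infer that the analysis has no protection at all; the first row of the table contradicts this. A reader might infer that the data of days 2–4 are discarded; pedometer and observation data from those days feed the coach feedback, and the article does not say that they are excluded from every analysis. A reader might infer a loss of precision from change scores; that belongs to a reading in which day 1 is also an outcome, needs a day-1-to-day-5 correlation that the article does not give, and concerns efficiency, not missing-data bias.

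**Conclusion.** The point holds in a limited form. For the analysis that Trial design and Statistical analysis describe, the mixed model offers no protection against missing-data bias beyond that of a complete-case ANCOVA, so the stated justification overclaims. This follows from the structure of the model and needs no assumption about the data.

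The size of any bias is a different matter. The documents give neither correlations between days nor a dropout mechanism. Eight players is a planning allowance, not a forecast. The errors of 0.045 to 0.075 show that an effect is possible under assumed correlations and dropout that acts differently by arm. They do not estimate what will happen in this trial.

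Using all five days widens the range of dropout that can be handled to that explained by observed activity on days 2–4. It does not cover dropout that depends on the unseen day-5 value, so the quoted sentence would still be too strong even for the better model. The gain is confined to outcomes recorded daily. For motivation and autonomy support no intermediate data exist.

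**What to change.** For accelerometer-measured MVPA and inactivity, specify one likelihood-based longitudinal model for training-session data from days 1–5. Include day and arm-by-day terms, with the arms constrained equal on day 1; this is justified because randomisation followed the baseline assessments. Keep the day-5 arm contrast as primary. State that the analysis assumes dropout depends on observed data only, and word the claim accordingly.

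For motivation and autonomy support, describe the analysis as a complete-case, baseline-adjusted comparison and delete the robustness claim. Modelling days 1 and 5 jointly is no substitute, since it gave the same answers as ANCOVA to within 0.001.

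The cost is the extraction of training-session data for days 2–4, for which session times were recorded, and a covariance structure to be specified in advance. No new data or players are needed. Whether coach or site effects belong in the model is a separate question that this change does not settle.

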## Discussion

A number of studies have recently been published examining OYS clubs as a setting to promote health [51-53]. These studies illustrate the wide range of health-promoting capabilities OYS can provide and the importance of OYS clubs, yet, only one study has acknowledged that OYS clubs could play a role in promoting physical activity [53]. Studies have shown that children and adolescents can accumulate considerable amounts of MVPA during OYS; however, the majority of time spent during OYS is either inactive or in a light physical activity intensity [6,7,12]. Thus, there is clearly an opportunity to optimise MVPA levels and reduce inactivity and light physical activity during OYS. If the intervention is successful, this study’s findings will support the use of coach education sessions to increase MVPA in OYS, which can have major public health implications given the high proportion of children and adolescents who participate in OYS globally [1-4].

This study is not without its limitations. First, this study only investigated the short-term efficacy of coach education on player physical activity as the basketball program took place over five consecutive days. Further, by conducting this study as an OYS basketball program (rather than using players’ usual competition teams and coaches) may have limited our generalisability; however, it has increased our internal validity by allowing us to test the efficacy of the intervention in a more tightly controlled environment. The decision to conduct this study in the form of an OYS basketball program (rather than using players’ usual competition teams and coaches) was made to allow us to individually randomise players to different training groups and coaches within their allocated arm each training session period. If this study were conducted in players’ usual competition, sampling would have had to take place on three levels (player, coach, OYS club), each additional level, an additional source of sampling error causing power to drop. By forming an OYS basketball program and individually randomising players to different training groups and coaches, we avoided a clustering effect and thus a cluster randomised controlled trial study design that would require a much larger sample. Studies conducted in a similar setting have observed high intra-class correlations for MVPA (indicating a large clustering effect) [45,54]. Our sample size, then, would have been inflated considerably to reach sufficient power and account for the clustering; which would not have been feasible. Despite this limitation, the present study employed a rigorous study design and used a high-resolution (1-second epochs) objective measurement to assess physical activity. Additionally, this study will provide insight on girls’ motivation, lesson context and leader behaviour (through SOFIT).

The current trial protocol presents, as far as we are aware, the first intervention to be conducted in an OYS context designed to investigate the efficacy of coach education sessions (relative to a no-treatment control) on increasing players’ MVPA and reducing inactivity during training. If the intervention is successful, this study’s findings will support the use of coach education sessions to increase MVPA in OYS; thus, this study’s protocol can be used as a starting point to inform future interventions and strategies to increase MVPA and reduce inactivity during OYS.

## Abbreviations

MVPA: Moderate-to-vigorous physical activity; OYS: Organised youth sport; RCT: Randomised controlled trial; SDI: Self-determination index; SOFIT: System for Observing Fitness Instruction Time; UWS: University of Western Sydney.
